### Interim Analysis and Stopping Guidance

As a risk to participants in FLUID is minimal, and given the delayed availability of data from the Ontario provincial health administrative databases needed for outcome assessment, no interim analyses are planned in the FLUID trial.

### Adherence and Protocol Deviations

Protocol adherence will not be measured at the individual patient level. Adherence will be measured according to the aggregate use of the study fluid throughout the hospitals using the hospital inventory system. Adherence will be monitored at 2-week intervals over the study period and reported according to each study group across all participating hospitals, combined and according to major fluid user groups in specific settings (ED, surgery, medicine, operating room, ICU, postoperative assessment unit, and obstetrics). Overall adherence will be defined as the total use of the allocated study fluid divided by the total combined use of NS and RL.

### Participant Withdrawal

We will not be collecting individual patient-level data, as all data will be collected through the ICES provincial database. As informed consent is not being sought, only clinically available data are being analyzed, and no unique research data are being collected, participants cannot withdraw from the study.

### Participant Follow-Up

We anticipate near 100% follow-up since all clinical data and outcome measures from participating sites in Ontario will be available at ICES, except for a very small number of patients who leave the province of Ontario within 90 days after enrollment.

### Data Sources

Data will be obtained and housed using Ontario’s population-based health administrative databases at ICES. ICES is an independent, nonprofit research institute whose legal status under Ontario’s health information privacy laws allows the collection and analysis of health care and demographic data. The data sets identified in Table 2 were linked using unique identifiers and analyzed at ICES.

**Table 2 table2:** ICES data sources.

Database	Acronyms
Registered Persons Database	RPDB
Discharge Abstract Database	DAD
Ontario Mental Health Reporting System	OMHRS
National Ambulatory Care Reporting System	NACRS
Ontario Health Insurance Plan	OHIP
Same Day Surgery	SDS
Ontario Drug Benefit	ODP
OHIP lab claims	All OHIP billings have a fee code beginning with “L”
OHIP physician billings	N/A^a^
Home Care Database	OACCAC^b^ HCD
Complex and Continuing Care	CCRS
National Rehabilitation System	NRS
Continuing Care Reporting System	CCRS
Family Health Organization or Family Health Network Capitation	FHO or FHN
Long term care	N/A
National Ambulatory Care Reporting System visits to hospital outpatients clinics and dialysis clinics	NACRS
National Ambulatory Care Reporting System visits to cancer clinics	NACRS
New Drug Funding Plan chemotherapy drugs	NDFP
Assistive Device program	ADP

^a^N/A: not applicable.

^b^OACCAC: Ontario Association of Community Care Access Centres.

### Timing of Final Analysis

All follow-up and data collection for patients at the participating sites will be captured by ICES. The approach to analysis will be supervised by the study statistician and principal investigator; however, the final analysis will be conducted by an independent statistician not involved as a coinvestigator in the FLUID trial.

### Statistical Principles

#### Analytical Framework

All study outcomes will be tested for superiority.

#### CIs and *P* Values

All statistical tests will be 2-sided and performed using a 5% significance level. We will report all CIs as 95% and 2-sided. Results will be expressed as absolute differences produced by analyses described below.

#### Analysis Populations

Our primary analysis will use the intention-to-treat approach and will include all enrolled patients in the treatment groups to which their cluster was randomized at the time of the index hospitalization. Because true fluid exposure status is not recorded in administrative databases, all admitted patients will be included in the analysis, regardless of actual fluid administration.

#### Outcome Definitions

##### Primary Outcome

The primary outcome is a composite of death or readmission to the hospital within 90 days of the index hospitalization. All-cause death will be obtained at a patient level using the Registered Persons Database, while hospital readmission will be measured from Discharge Abstract Database (DAD). Cluster randomized trials can address 2 types of estimands: the participant-average or the cluster-average treatment effect [39]. The former estimates the effect of an intervention for an average participant, whereas the latter estimates the effect for an average cluster. In the FLUID trial, intervention exposure will be unknown at the individual patient-level and the primary study objective is to inform a decision by the health system stakeholder; thus, the primary estimand in the FLUID trial is the cluster-average treatment effect. It is known that cluster-average and participant-average treatment effects will differ when cluster sizes are informative, meaning that either the outcomes or treatment effects vary with cluster size. In the FLUID trial, it is possible that treatment effects will vary between larger or smaller hospitals, and thus, informative cluster sizes cannot be ruled out. The statistical analysis plan was therefore formulated to yield an unbiased estimate for the cluster-average treatment effect in the presence of informative cluster sizes.

##### Secondary Outcomes

The secondary outcomes are 90-day death, hospital readmission within 90 days of the index hospitalization, and requirement for new dialysis within 90 days; and for surgical patients, requirement for reoperation, postoperative reintubation in the postoperative assessment unit, ED visits within 90 days, hospital length of stay, and discharge to facility other than home. All secondary outcomes will be obtained at the patient level from DAD and National Ambulatory Care Reporting System.

##### Tertiary Outcomes

The tertiary outcomes relate to the health economic analyses and include the incremental cost per one death averted and incremental cost per one quality-adjusted life year (QALY) gained.

#### Analysis Methods

##### Descriptive Analyses

Baseline data will be collected and summarized as means and SDs for continuous variables or counts and percentages for categorical variables as shown in Table 3. We will summarize outcome data as cluster-period frequencies and proportions for dichotomous primary and secondary outcomes and medians with IQRs for the length of stay. Outcome data will be reported by the treatment group.

**Table 3 table3:** Baseline characteristics.

Characteristic				Total # index admissions		Normal saline		Ringer’s lactate
Sex, female, n (%)								
Age (years), mean (SD)								
**Age group, n (%)**								
	1 month to 18 years							
	>18 to 65 years							
	>65 to 80 years							
	>80 years							
**Case mix group, n (%)**								
	Medicine							
	Surgery							
	Pregnancy and childbirth							
	Mental health							
**Type of surgical admission, n (%)**								
	Elective							
	Urgent							
	Surgical admission<24 hours							
**Surgical subgroups**								
	General							
	Thoracic							
	Cardiac							
	Vascular							
	Orthopedic							
	Obstetrical							
	Gynecological							
	Ear or Nose or Throat							
	Plastic							
	Urological							
	Neurosurgery							
	Trauma							
	Other							
**Severity of illness, n (%)**								
	Admission to ICU^a^							
	Infection Alone and Infection and Organ Dysfunction							
	Infection Alone and Infection and Organ Dysfunction and ICU admission							
	**Trauma ISS^b^ ≥12, n (%)**							
		Trauma ISS≥12+ICU						
	**Traumatic brain injury, n (%)**							
		Traumatic brain injury+ICU						
**Comorbidities**								
	Elixhauser Comorbidity Score, mean (SD)							
**Elixhauser Comorbidities, n (%)**								
	Diabetes, complicated							
	Hypertension, uncomplicated, and complicated							
	Cardiac arrhythmias							
	Solid tumor without metastasis							
	Fluid and electrolyte disorders							
	Diabetes, uncomplicated							
	Congestive heart failure							
	Metastatic cancer							
	Chronic pulmonary disease							
	Other neurological disorders							
	Peripheral vascular disorders							
	Coagulopathy							
	Valvular disease							
	Obesity							
	Renal failure							
	Paralysis							
	Liver disease							
	Alcohol abuse							
	Pulmonary circulation disorders							
	Depression							
	Deficiency anemia							
	Lymphoma							
	Drug abuse							
	Rheumatoid arthritis or collagen vascular diseases							
	Hypothyroidism							
	Weight loss							
	Psychoses							
	Blood loss anemia							
	Peptic ulcer disease excluding bleeding							
	AIDS or HIV							

^a^ICU: intensive care unit.

^b^ISS: injury severity score.

##### Primary Analyses of the Primary and Secondary Outcomes

All analyses will be conducted according to recommendations for cluster randomized crossover trials, accounting for clustering to ensure correct type I error rates and CIs [38,40]. In the case of a small number of clusters, mixed-effects regression and generalized estimating equation approaches are known to not perform well; analysis for FLUID will, therefore, be performed using cluster-level summaries. This method is known to perform well even with a very small number of clusters. Equal weight will be given to each cluster to obtain unbiased estimates for the cluster-average treatment effect. To implement the cluster-level method, binary outcomes will be expressed as proportions in each cluster-period and the differences (proportion under RL minus proportion under NS will be calculated for each cluster. These differences will then be analyzed using an unweighted linear regression model as described by Turner et al [41]. The t-distribution with degrees of freedom equal to the number of clusters minus 2 will be used. The intervention effect will be expressed as an absolute difference with 95% CI. To improve precision, the primary analysis will account for the following patient risk factors as fixed effect covariates: age, sex, comorbidity index, type of hospital admission (medicine, surgery, pregnancy and childbirth, and mental health), and admissions to ICU, using the 2-stage method recommended by Hayes and Moulton [42]. Patient age will be modeled using a restricted cubic spline to allow for the possibility of a nonlinear association. Mean imputation within hospitals will be used for missing baseline covariates. The same approach and covariates will be used for primary and secondary outcomes. The 2-stage method will be implemented as follows: (1) a multivariable regression model (logistic regression for binary outcomes and linear regression for length of stay) with the baseline characteristics as covariates but excluding the treatment and cluster indicators will be fit to the individual patient data in period 1 and period 2. Length of stay will be log-transformed prior to analysis. We will use each regression model to obtain predicted probabilities for each binary outcome and predicted length of stay for each patient. (2) For binary outcomes, we will calculate the expected number of events by summing the predicted probabilities across all patients in that cluster period; for length of stay, we will obtain the expected mean length of stay by averaging across all patients in that cluster period. (3) We will obtain residuals for binary outcomes by calculating the observed number of events minus the expected number of events divided by the number of patients in the cluster, and for length of stay by calculating the observed mean minus the expected mean. To estimate the treatment effect, the cluster-level method described above will then be applied to the residuals. Estimated intracluster correlation coefficients will also be reported [33]. The data presentation is indicated in Table 4.

**Table 4 table4:** Study outcomes.

		Normal saline (control; n=XXX)	Ringer’s lactate (treatment; n=XXX)	Absolute difference (95% CI)	*P* value

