## Abstract

**Background:**

Normal saline (NS) and Ringer’s lactate (RL) are the most common crystalloids given to hospitalized patients. Despite concern about possible harm associated with NS (eg, hyperchloremic metabolic acidosis, impaired kidney function, and death), few large multicenter randomized trials focused on critically ill patients have compared these fluids. Uncertainty exists about the effects of these fluids on clinically important outcomes across all hospitalized patients.

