Crystalloid fluids are administered to the majority of patients admitted to the hospital and continued throughout their hospital stay. To address ongoing uncertainty on this topic, and address this evidence gap about fluid administered outside the ED and ICU, we designed a cluster randomized crossover trial. Our objective was to compare a hospital-wide strategy to preferentially stock NS or RL as the main crystalloid resuscitation fluid, aiming to have all admitted patients receive the allocated crystalloid from the time they enter hospital to hospital discharge, evaluating the primary composite outcome of death or readmission to hospital in the first 90 days. The design of the FLUID trial is novel because it involves a pragmatic cluster randomized crossover design, a waiver of patient informed consent to include all hospitalized patients, hospital-based randomization, and the use of routinely collected electronic health administrative data for the description of baseline characteristics and all study outcomes. FLUID will generate data at low risk of bias, providing key evidence about the consequences of crystalloid fluid on clinically important outcomes, and informing patient care and health care policy. It will also provide insight into a novel approach to the conduct of large pragmatic clinical trials.

This manuscript describes the protocol and statistical analysis plan for the evaluation of primary and secondary outcomes for the FLUID trial.

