##### Subgroup Analyses

The primary outcome will be analyzed within the following subgroups of patients who are at a higher risk for exposure to fluids and with greater risk profiles and or severity of illness than other patients. These include age (<18, 18 to ≤65, 66 to ≤80, and >80 years); sex; type of hospital admission (medical, surgical, pregnancy and childbirth, mental health); elective and urgent or emergent surgical admissions, surgical admissions <24 hours, surgical subgroups (as described in Table 3); admission to ICU, infection alone and infection and organ dysfunction, infection alone and infection and organ dysfunction and ICU admission, trauma with injury severity score (ISS) ≥12, trauma with ISS=12 and ICU admission, traumatic brain injury, traumatic brain injury and ICU admission, and comorbidity index (Elixhauser) [43]. These subgroup analyses will be implemented without covariate adjustment and using the cluster-level summary method as described for the primary and secondary outcomes but applied to subgroup differences within each cluster. Results will be presented using forest plots.

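### The primary model adjusts for ICU admission and an Elixhauser index that are not limited to status before fluid exposure, so an effect running through them could be removed

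*Protocol article*

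**What the plan says.** In the Protocol article, the section *Primary Analyses of the Primary and Secondary Outcomes* gives the purpose of adjustment: "To improve precision, the primary analysis will account for the following patient risk factors as fixed effect covariates". The covariates are "age, sex, comorbidity index, type of hospital admission (medicine, surgery, pregnancy and childbirth, and mental health), and admissions to ICU", and the same set serves every primary and secondary outcome. Stage 1 is a regression "with the baseline characteristics as covariates but excluding the treatment and cluster indicators will be fit to the individual patient data". Observed minus expected events per patient are then compared between fluids within each hospital.

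The Introduction describes the strategy as "aiming to have all admitted patients receive the allocated crystalloid from the time they enter hospital to hospital discharge". The section on adherence names the emergency department (ED) and the operating room among the settings where fluid use is tracked.

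Table 3 lists ICU admission under severity of illness, without a time window. Its Elixhauser items include "Fluid and electrolyte disorders" and "Renal failure". The Background of the Abstract names the suspected harms of normal saline (NS) as "hyperchloremic metabolic acidosis, impaired kidney function, and death", and the Introduction names metabolic alkalosis as a possible effect of Ringer's lactate (RL). The subgroups for the primary outcome include "admission to ICU, infection alone and infection and organ dysfunction".

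**The concern.** A covariate used to gain precision must be fixed before it can be influenced by the treatment. Here the hospital's fluid is set before the patient arrives, and fluid may be given in the ED or operating room before any ICU transfer. ICU admission without a time limit therefore includes transfers that come after exposure. The text calls the covariates baseline characteristics, but no definition secures that label.

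The comorbidity index raises the same question in a weaker form. No rule states whether its items come from earlier records or from diagnoses coded during the index stay. If the latter, an electrolyte or renal diagnosis caused by the fluid would count as a comorbidity.

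At stake is what the primary estimate means. The trial asks for the total effect of a stocking policy on death or readmission. An estimate that excludes any part acting through ICU transfer or coded disorders answers a narrower question. The same covariates are used for new dialysis and length of stay. The subgroups are analysed without covariate adjustment, but the fluid could still change who enters the ICU and organ-dysfunction subgroups.

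**Working it through.** **1. The plan's own figure.** Inputs from *Sample Size*: event proportion 0.16 under NS, a 1-point difference (so 0.15 under RL), within-period ICC 0.006, cluster autocorrelation 0.95, and 1500 patients per month (about 4500 per period).

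- Variance of one hospital's difference = 2 × p(1−p) × [(1−ICC)/m + ICC × (1−CAC)].
- Average p(1−p) = (0.1344 + 0.1275)/2 = 0.13095.
- Bracket = 0.994/4500 + 0.006 × 0.05 = 0.000221 + 0.000300 = 0.000521.
- Variance = 2 × 0.13095 × 0.000521 = 0.0001364.
- Sites = 0.0001364 × (1.960 + 0.842)² / 0.01² = 10.7, or 12 when rounded up to an even number.

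This agrees with the stated 12 sites if the 1 point is already net of nonadherence, so the same variance can be used below.

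**2. What the two-stage method removes.** Stage 1 omits treatment, so expected events differ between fluids wherever the covariates differ. To first order:

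amount removed = (difference between fluids in the covariate mean) × (covariate slope).

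If the fluid does not affect the covariate, this is zero.

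**3. ICU admission.** The documents give no ICU rate, no risk in ICU patients and no effect of fluid on ICU admission. Assumed: ICU rate 5-15% under NS, 90-day event risk in ICU patients 30-40%, overall risk 16% under NS, true total effect −1.0 point.

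Worked case (ICU rate 10%, ICU risk 40%, RL lowers ICU admission by 1.0 point):

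- Non-ICU risk under NS = (0.16 − 0.10 × 0.40)/0.90 = 0.1333.
- Risk under RL from the ICU shift alone = 0.09 × 0.40 + 0.91 × 0.1333 = 0.1573. A further −0.0073 in both strata is needed to reach 0.15.
- Pooled ICU risk = (0.10 × 0.40 + 0.09 × 0.3927)/0.19 = 0.3965. Pooled non-ICU risk = (0.90 × 0.1333 + 0.91 × 0.1260)/1.81 = 0.1296. Slope = 0.2669.
- Removed = 0.01 × 0.2669 = 0.0027. The adjusted estimate is −0.73 point, a loss of 26.7%.

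For power with 16 sites, p(1−p) is taken as 0.1344: variance = 2 × 0.1344 × 0.000521 = 0.000140, standard error = √(0.000140/16) = 0.00296, t on 14 degrees of freedom. The standard error is held fixed, so any precision gained by adjustment is ignored.

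| Fall in ICU admission under RL (points) | Share of effect removed | Power |
|---|---|---|
| 0 | 0% | 88% |
| 0.25 | 4-7% | 83-86% |
| 0.5 | 7-14% | 77-83% |
| 1.0 | 15-28% | 62-76% |

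If RL instead raised ICU admission by 1.0 point with the same total effect, the estimate would be exaggerated by 15-28%, reaching about −1.15 to −1.28 points.

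**4. Comorbidity index.** The plan enters one index, whose scoring is not stated. Assume one point per item and a slope of 3-5 percentage points of risk per index point. A 1-point difference in coded fluid and electrolyte disorders shifts the mean index by 0.01 and removes 0.01 × 0.03 to 0.01 × 0.05, that is 0.03-0.05 point (3-5% of the effect). A 2-3 point difference removes 0.02 × 0.03 = 0.06 to 0.03 × 0.05 = 0.15 point (6-15%). If the index is built only from earlier records, the figure is zero.

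**5. What ICU adjustment buys.** Assume 10% in ICU and a 20-point risk difference. ICU then explains 0.10 × 0.90 × 0.20² / 0.1344 = 2.7% of patient-level variance. Patient-level sampling is 0.000221/0.000521 = 42% of the variance of a hospital's difference, so the gain is about 0.42 × 2.7% = 1.1%. Case-mix shifts between periods could add to it.

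**The case against.** The plan calls these variables baseline, and Table 1 ticks comorbidities and severity at enrolment. Most Elixhauser items are chronic conditions, and a look-back rule is the kind of operational detail a condensed article leaves out. Median stay is 2 days and the population includes mental health and obstetric patients, so a hospital-wide shift of a full point in ICU admission would be large against a 1-point target. Evidence cited in the Introduction is mixed: two single-centre trials found fewer kidney events with balanced fluid, while two multicentre trials and a systematic review found no renal difference. Table 3 would show imbalance in ICU admission and in each comorbidity, and Table 4 gives crude proportions by fluid.

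Much of this stands for the comorbidity index, where the concern is conditional on the look-back. It does not settle ICU admission, because the covariate is fixed in the text without a time limit. Table 4 has a single column for the absolute difference, and the sensitivity analyses include no run without these covariates, so readers would see an imbalance but not its consequence for the estimate.

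Three stronger readings are tempting and not supported:

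- That Table 1 is in error because it places these data before allocation. The same column holds demographics and case mix, which are ordinary patient baseline data.
- That about half the effect could be lost. Reaching that needs electrolyte disorder as a separate covariate with a slope of about 15 points, under which a 2-3 point shift removes 0.30-0.45 point. The plan uses one index.
- That the bias must run toward no difference. The Introduction names possible harms of both fluids, so it may run either way.

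**Conclusion.** The point holds in conditional form. The plan adjusts its primary estimate for ICU admission, which can follow exposure, and for an index not limited to diagnoses made before the stay. Any effect of the fluid through them would be removed. A reader might infer that these variables do arise after exposure and that part of the effect will be lost. The documents show neither: the look-back is unstated, and no figure is given for an effect of fluid on ICU admission or coding.

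Under the assumed ICU rates and risks, the distortion is nil with no fluid effect on ICU admission and 4-28% of a 1-point effect for a shift of 0.25-1.0 point, in either direction. The index route is probably smaller and depends on scoring and look-back. ICU admission is the firmer half. This is a cheap improvement that should be made, not a fatal flaw.

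**What to change.** - Drop ICU admission from the covariates for the primary and secondary outcomes. Restricting it to direct ICU admission on presentation is only a partial remedy, since fluid given in the ED can come first.
- Compute the Elixhauser index only from ICES records dated before the index admission, and state the look-back window. With that rule the index need not be altered item by item.
- Report the unadjusted cluster-level estimate with its 95% CI beside the adjusted one in Table 4.
- Label the ICU and infection-with-organ-dysfunction subgroups as defined after randomisation, by events that may follow exposure, and interpret them accordingly.

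The cost is a change of wording and a look-back query in linked ICES data. The article states that the trial data set had not been received, so the change could be made without knowledge of results. The downside is slightly less explained variance: about 1% of the variance of each hospital's difference for ICU admission under the assumptions above, and possibly some loss from a comorbidity index without diagnoses from the current stay.

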### Sample Size

A total of 16 hospital sites (including the 4 pilot sites) will yield data on approximately 144,000 hospital admissions. It required 12 sites in a 2-period cluster crossover trial over 6 months to achieve 80% power with a 2-sided α of 0.05 to detect a minimum clinically important absolute difference of 1% in the primary outcome in favor of RL, assuming a proportion of 0.16 in the NS condition, a within-period intracluster correlation coefficient of 0.006, a cluster autocorrelation coefficient of 0.95, and an average of 1500 patients per hospital per month [37]. These estimates were calculated from available routinely collected data for January 1 to December 31, 2013, for all eligible hospitals across the province of Ontario, Canada. Our calculations account for nonadherence based on pilot data (94% adherence NS, 80% RL). We added 2 clusters as an approximate small sample correction [38] and a further 2 to account for cluster size variation [38], for a final sample size of 16 sites.

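### The stage-1 adjustment set pools all surgery into one level and leaves out elective versus urgent surgical status: a missed precision gain, small for the primary outcome and modest for the surgery-only outcomes

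*Protocol article*

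**What the plan says.** Under Primary Analyses of the Primary and Secondary Outcomes, the article gives the purpose and the list of covariates: "To improve precision, the primary analysis will account for the following patient risk factors as fixed effect covariates", namely "age, sex, comorbidity index, type of hospital admission (medicine, surgery, pregnancy and childbirth, and mental health), and admissions to ICU". It then extends the list: "The same approach and covariates will be used for primary and secondary outcomes". The stage-1 model is a patient-level regression "with the baseline characteristics as covariates but excluding the treatment and cluster indicators". The residuals are reduced to cluster-period summaries and compared on a t-distribution with clusters minus 2 degrees of freedom, which is 14 for 16 sites.

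Three other places bear on this:
- Table 3 has a row group headed "Type of surgical admission, n" with levels elective, urgent and under 24 hours, and a separate 13-level list of surgical subgroups.
- Subgroup Analyses uses "elective and urgent or emergent surgical admissions, surgical admissions <24 hours, surgical subgroups (as described in Table 3") as factors for the primary outcome.
- Secondary Outcomes includes, "for surgical patients, requirement for reoperation, postoperative reintubation in the postoperative assessment unit", without defining which admissions make up that denominator.

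**The concern.** The only stated reason for adjustment is precision, and the article presents itself as the analysis plan, so the covariate list is a fixed choice. Within surgery, urgency is settled at admission and plausibly separates low-risk from high-risk patients. The plan itself treats the item as related to risk, by using it for subgroups and by excluding short elective surgical stays in a sensitivity analysis. A hospital's mix of elective and urgent surgery can also change between two periods about 15 weeks apart. Any part of that change that is specific to the hospital, and not captured by the other covariates, stays in the residual variation of a comparison with 14 degrees of freedom.

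The surgery-only outcomes are the sharper case. If surgical patients are exactly the surgery case mix group, admission type is constant for them and drops out. What is at stake is the width of confidence intervals, mainly for two secondary outcomes.

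**Working it through.** **The plan's own figure first.** Inputs from Sample Size: "80% power with a 2-sided α of 0.05", proportions 0.16 and 0.15, ICC 0.006, cluster autocorrelation 0.95, and 1500 patients per hospital per month, so m = 3 × 1500 = 4500. Two proportions need 20,559 patients per condition. The design effect is 1 + (m − 1)(0.006) − m(0.006)(0.95) = 2.344. Sites = 20,559 × 2.344 / 4500 = 10.7, and the next even number is the stated 12 (reading the 1% as the difference actually analysed). 16 × 1500 × 6 = 144,000, as stated. The point here does not depend on this figure, but the same ICC inputs feed the next step.

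**Primary outcome, baseline variance.** Twelve weeks give 1500 × 12/52 × 12 = 4154 patients per cluster-period. The variance of one hospital's RL-minus-NS difference is 2p(1 − p)[(1 − ICC)/m + ICC(1 − CAC)] = 2(0.1344)(0.000239 + 0.0003) = 0.000145. The SE over 16 hospitals is √(0.000145/16) = 0.30 percentage points.

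**Contribution of a shift in elective share.** Assumed, since the documents give no values: 30% of admissions surgical, event risk 8% elective and 20% urgent. A between-period change in elective share with standard deviation s adds (0.30 × 0.12 × s)² to that variance.

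| s (points) | Added variance | Share of 0.000145 | Simulated SE, without → with urgency | SE cut |
|---|---|---|---|---|
| 3 | 0.0000012 | 0.8% | 0.302 → 0.301 | 0.3% |
| 5 | 0.0000032 | 2.2% | 0.303 → 0.299 | 1.3% |
| 10 | 0.0000130 | 8.9% | 0.317 → 0.303 | 4.4% |

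The SE columns come from 6000 simulated trials per scenario of the two-stage method; the formula and the simulation agree. For a 1-point difference (t, 14 df), power moves from 86.8% to 87.0%, from 86.6% to 87.5%, and from 83.5% to 86.6%.

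**A second route.** With surgical share 25–35%, elective share 50–60%, elective risk 6–8% and urgent risk 16–24% (all assumed), urgency explains 0.3% to 2.1% of patient-level variance over all admissions. Patient-level variance is 42% of the variance of the contrast at m = 4500 (0.994/2.344), so by this route the SE falls by at most 1 − √(1 − 0.42 × 0.021) = 0.45%. If urgency also explained an assumed 10% to 25% of the cluster-by-period variance, the SE would fall by about 3% to 7.5%. That variance is 2(0.1344)(0.0003) = 0.0000806, so with the risk gap above those shares need s = √(0.10 × 0.0000806)/0.036 = 7.9 points and, likewise for 25%, 12.5 points. The larger gains therefore again require large shifts.

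**Reoperation.** Assumed: 1250 surgical patients per cluster-period, risk 3% elective and 8% urgent. Simulated SEs are 0.231 → 0.227, 0.232 → 0.223 and 0.259 → 0.224 points for s = 3, 5 and 10, cuts of 1.7%, 3.9% and 13.5%. Check at s = 5: the added variance is (0.05 × 0.05)² = 0.00000625 and the adjusted variance is 16 × 0.00223² = 0.0000796, a ratio of 7.9%, consistent with the simulation. The level depends on how the ICC is carried to this outcome. With 60% elective, the mean risk is 0.6 × 3% + 0.4 × 8% = 5%, and the primary outcome's ICC and autocorrelation give 2(0.0475)(0.994/1250 + 0.0003) = 0.000104 (SE 0.255 points). The ratio is then 6.0% and the SE cut 2.9%; at s = 3 the cut is 1.1%.

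**The admission-type factor.** A factor with one level is aliased with the intercept. Refitting a logistic model with such a factor changed fitted values by at most 3 × 10⁻¹⁵, so it does no harm and contributes nothing.

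**The case against.** The strongest reply is that nothing here is wrong. A prognostic set is prespecified, each hospital receives both fluids, and a single list for all outcomes limits data-driven choice. That stands: a reader might infer that the primary analysis is biased or inconsistent, and the documents do not support it.

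The reply also weakens the numbers. As described, the simulated comparison contrasts stratum means with and without urgency and does not include age, sex, comorbidity or ICU admission. The plan already adjusts for all four, and they would absorb part of any shift, so the gains are nearer an upper bound. Changes shared by sites running at the same time would be balanced in the point estimate by randomizing in batches of 4 with blocks of 2. Nothing in the documents supports a 10-point SD. All of this stands.

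Two stronger readings also fail. It is tempting to say that admission type is constant in the surgical outcomes, but the denominator is undefined: Table 3 lists obstetrical among the surgical subgroups while pregnancy and childbirth is a separate case mix group, so the factor may still vary. Even then it would separate obstetric from other surgery, not elective from urgent. It is also tempting to say that these outcomes receive no case-mix adjustment; they lack only a surgery-specific term. Finally, urgency is recorded for surgical admissions only, so it is not an admission-wide covariate that was overlooked.

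The reply does not remove the fact that an item already in hand, and treated by the plan as risk-related, is unused where it would be most informative.

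**Conclusion.** The point holds as a low-cost refinement. The adjustment set merges all surgery and is carried unchanged to outcomes limited to surgical patients, leaving them without a surgery-specific term. For the primary outcome the loss is about 0% to 1.5% of the SE, unless elective share shifts within hospitals by something like an SD of 10 points. For reoperation it is about 2% to 4% in the milder scenarios, and 1% to 3% if the primary outcome's ICC is applied directly at a 5% mean risk. Overlap with existing covariates would probably reduce both. Surgical share, risks, shifts and every reoperation input are assumptions, and reintubation was not simulated. The case rests mainly on the two surgical outcomes.

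**What to change.** Before the data are received, replace the surgery level of the stage-1 admission-type factor by two levels, elective surgery and urgent surgery, for all outcomes. In reoperation and reintubation this split then becomes the working admission-type term. State at the same time which admissions form the surgical denominator, including whether obstetrical surgery counts.

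Do not enter the category for stays under 24 hours as a covariate, because it is defined by the observed stay; those admissions should be classed by their elective or urgent status. Do not require the 13-level surgical subgroup. Its benefit has not been examined, and in a possibly rare outcome it could produce empty cells and separation; use it only in collapsed form and only if event counts support it.

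The cost is one or two sentences and a recode. The article states that the plan precedes receipt of the data set, so the change can still be prespecified. It needs no new data, and because stage 1 is fitted to patients, the 14 cluster-level degrees of freedom are untouched.
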